## Abstract

**Background:**

The National Comprehensive Cancer Network Breast Cancer Guidelines Committee suggests that the omission of adjuvant radiation therapy (RT) after breast-conserving surgery can be a reasonable option among older women with low-risk breast cancer (early-stage, estrogen receptor-positive, and node-negative) if they are treated with endocrine therapy. However, RT usage in this group of women still exceeds 50%. Conversely, older women tend to forego RT (even when necessary) due to cost, inconvenience, and potential adverse responses associated with RT. Understanding health-related quality of life (HRQOL) change with receipt of RT among older women in the modern era is limited due to the under-representation of this population in clinical trials.

**Objective:**

The proposed study aims to examine the associations of RT with HRQOL trajectories as well as survival outcomes among older women with 5-10 years of follow-up. We will also assess whether prediagnosis comorbidity burden influences receipt of RT and whether the associations between RT and HRQOL trajectory and survival outcomes are modified by the comorbidity burden.

**Methods:**

We will use a retrospective cohort study design with the population-based Surveillance, Epidemiology, and End-Results database linked to the Medicare Health Outcomes Survey (SEER-MHOS). Older women (≥65 years) who were diagnosed with low-risk breast cancer in 1998-2014, received breast-conserving surgery, and participated in MHOS 1998-2016 are eligible for this analysis. The latent class analysis clustering method will be used to identify each patient’s prediagnosis comorbidity burden, and HRQOL will be evaluated using the Short Form 36/Veterans RAND 12-Item Health Survey scales. The inverse-weighted estimates of the probability of treatment will be included to control for treatment selection bias and confounding effects in subsequent analysis. The association of RT with HRQOL trajectory will be evaluated using inverse-weighted multilevel growth mixture models. The inverse-weighted Cox regression model will be used to obtain hazard ratios with 95% CIs for the association of RT with survival outcomes. Differential effects of RT on both outcomes according to comorbidity burden class will also be evaluated.

**Results:**

As of October 2020, the study was approved by the institutional review board, and SEER-MHOS data were obtained from the National Cancer Institute. Women with low-risk breast cancer who met inclusion and exclusion criteria have been identified, and prediagnosis comorbidity burden class has been characterized using latent class analysis. Further data analysis will begin in November 2020, and the first manuscript will be submitted in a peer-reviewed journal in February 2021.

**Conclusions:**

This research can potentially improve clinical outcomes of older women with low-risk breast cancer by providing them additional information on the HRQOL trajectories when they make RT treatment decisions. It will facilitate informed, shared treatment decision making and cancer care planning to ultimately improve the HRQOL of older women with breast cancer.

**International Registered Report Identifier (IRRID):**

DERR1-10.2196/18056

## Introduction

Breast cancer is the most prevalent cancer and the second leading cause of cancer-related deaths in American women [1]. Due to the aging of the female population and the increasing incidence of breast cancer with age [2], the number of older women with breast cancer continues to grow. Older women diagnosed with early-stage breast cancer have multiple locoregional treatment options depending on prognostic factors such as tumor type and disease stage. Adjuvant radiation therapy (RT) following breast-conserving surgery (BCS) is standard treatment for early-stage breast cancer, as this course of treatment improves clinical outcomes significantly [3,4]. Older women are often concerned with potential health-related quality of life (HRQOL) declines associated with cancer treatment [5]. These concerns of older women can present clinical challenges when making treatment decisions considering the pros and cons of adjuvant RT within the context of life expectancy.

Many randomized controlled trials (RCTs) have focused on the cancer care of older women. One of them is the CALGB 9343 trial, which reported that the recurrence rates of older women with estrogen receptor (ER)-positive early-stage breast cancer who received endocrine therapy alone were not significantly different from those of women who received both endocrine therapy and RT (4% vs 1%) [6]. Moreover, no significant survival benefits were observed with the addition of RT to endocrine therapy compared to endocrine therapy alone [6]. These remarkable results from the CALGB 9343 trial led to a change in the National Comprehensive Cancer Network (NCCN) Breast Cancer Guidelines in 2004, which suggested the omission of RT as a reasonable option for older women with low-risk breast cancer (early-stage, ER-positive, and node-negative) if they are treated with endocrine therapy [7]. Additionally, 10-20 years of long-term follow-up results of early RCT studies, such as CALGB9343, PRIME II, and BASO II, have further confirmed that adjuvant RT can be omitted in older women with favorable early-stage ER-positive, node-negative breast cancer [8-10].

Despite the aforementioned guideline update, the treatments of older women with low-risk breast cancer vary widely. In prior studies, the patterns of RT omission were not consistent across institutions, even at NCCN member institutions [11-13]. More importantly, RT usage in this group of women still exceeds 50% [14]. A recent survey reported that high proportions of surgeons and radiation oncologists erroneously overestimated survival benefits associated with RT in this group of women [15] because the estimation of life expectancy in older women is not straightforward [11]. Many treatment-decision algorithms include age to estimate life expectancy, but chronological age is not always correlated with one’s biological age and mortality. Including geriatric assessment in the algorithm improved compliance with NCCN guidelines without diminishing survival benefits [16]. Since accompanying comorbid conditions at diagnosis are strongly associated with mortality regardless of age [17-19], considering comorbidity burden in addition to age and tumor characteristics will improve the selection of women who can omit RT.

On the other hand, some older women tend to forego RT (even when necessary) due to cost, inconvenience, and uncertainty of potential adverse responses associated with RT. Limited evidence suggests that older women are more concerned about HRQOL declines rather than fear of recurrence when they make treatment decisions [20,21]. However, understanding HRQOL change with the addition of RT among this population is limited due to the under-representation of older women and those with comorbidities in clinical trials [22,23]. Many studies have evaluated adverse effects on HRQOL with receipt of RT, but most of them were cross-sectional designs or assessments of short-term changes within 1 year post RT [18,24-28]. Not many studies have evaluated the long-term effects of RT on HRQOL. In an older study, Lundstedt and colleagues reported that 10.3% of women had weekly pain even after 10-17 years of RT, and this observation was significantly higher among women who received adjuvant RT than those who did not (1.7%, *P*=.001) [29]. Therefore, we need to update long-term HRQOL with more data since there have been many advancements in RT techniques over the past 3 decades. Moreover, baseline HRQOL is a major predictor of subsequent HRQOL; thus, longitudinal evaluation of HRQOL trajectory in a cohort study design, rather than a cross-sectional evaluation of post-treatment HRQOL, will provide more valid estimates of the impact of RT on HRQOL.

Few studies have investigated the effect of RT among older women with varying comorbidity burden, and to our knowledge, none of the previous studies have evaluated long-term HRQOL trajectories post RT within older women treated in the modern era. Thus, the proposed study aims to examine the effects of RT on long-term HRQOL trajectories and survival outcomes among older women with low-risk breast cancer in an observational setting. Minimizing the potential bias due to treatment selection and controlling for potential differences in confounding factors between treatment groups are essential in observational comparative effectiveness studies without randomized treatment [30]. To mitigate this concern, first, we will only select older women with low-risk breast cancer whose main treatment plan includes BCS and endocrine therapy with RT being an option. Among this group of women, only 3.3% undergo chemotherapy [1]; thus, the confounding effect of chemotherapy on HRQOL and survival outcomes is minimal. Second, to further balance out the potential confounding factors between the 2 groups, we will use inverse probability of treatment weighting (IPTW) methods, a type of propensity score analysis [31-34], which we have applied successfully in other projects [35,36]. All potential confounding variables will be included in the statistical models when deriving the weights for each group.

This comparative effectiveness study will utilize a national sample of older women to provide much-needed evidence regarding the combined effects of RT and comorbidity on HRQOL (subjective outcome) and survival (objective outcome) in older women. This research has 2 aims.

Regarding Aim 1, we will examine the effect of RT on the HRQOL trajectory over time and its interaction with comorbidity burden in older women with low-risk breast cancer (n=465) using IPTW-adjusted growth mixture models. We hypothesize that the HRQOL trajectory will differ by treatment status and comorbidity burden, and the largest decline will be observed in older women with the highest comorbidity burden.

Regarding Aim 2, we will examine the effect of RT on 5-year mortality and its interaction with comorbidity burden in older women with low-risk breast cancer (n=634) using Kaplan-Meier survival analysis and a IPTW-adjusted Cox regression model. We hypothesize that receiving adjuvant RT will improve 5-year mortality, but the magnitude of improvement will differ by comorbidity burden class. We expect that women who have the lowest comorbidity burden and also receive RT will experience the greatest improvement in survival outcomes.

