#### Statistical Analysis Plan

Regarding the descriptive analyses, the baseline characteristics of the study population will be described in terms of the mean and SD for continuous variables and frequencies with percentages for categorical variables. Descriptive analyses will be conducted to compare demographic, tumor-related, and treatment-related factors for the study population by their treatment status (BCS and RT vs BCS only). Differences in continuous variables and categorical variables will be assessed by *t* tests and chi-square tests, respectively. All analyses will be conducted using SAS 9.4 (SAS Institute Inc.) and R 4.0.1 (R Core Team), and a 2-tailed α level of .05 will denote statistical significance.

The probability of the treatment received by a particular person will be estimated by generalized boosted models using receipt of RT as the dependent variable and the baseline characteristics, such as age at diagnosis, race/ethnicity, smoking status, income, education, SEER region, rurality, disease stage, tumor grade, tumor subtype, and year of diagnosis, as the independent variables. Then, the inverse of the probability of receiving the treatment the patient actually received conditional on the observed covariates will be calculated and included as a weight for each patient in subsequent analyses [41]. Balances in potential confounding factors between the treatment groups will be assessed using diagnostic tools, including chi-square tests for categorical variables, *t* tests for continuous variables, and the standardized mean differences between 2 groups [42]. The standardized mean difference will be calculated as the difference in means or proportions divided by a pooled estimate of SD. A standardized mean difference≥10% will be considered as evidence of imbalance [43].

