#### Measurements

The exposure variables are the same as those of Aim 1, namely BCS alone and BCS with adjuvant RT. We will consider vital status and cause of death as the outcomes. The main outcome for Aim 2 will be mortality (all-cause mortality and breast cancer-specific mortality considering nonbreast cancer mortality as a competing event). The SEER data file provides the vital status of participants and the date and causes of death, which have been verified through the National Death Index. Survival will be calculated from the date of diagnosis to the last known follow-up date or December 31, 2016, whichever comes first. As in the case of Aim 1, the comorbidity burden will serve as the effect modifier. The confounding factors will match those of Aim 1.

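### Aim 2 hypothesises a survival benefit of RT that the cited trials did not show, and plans no analysis that would tell such a benefit from fitter women being chosen for RT

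*Protocol article*

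**What the plan says.** The Aim 2 paragraph of the Introduction sets the direction: "We hypothesize that receiving adjuvant RT will improve 5-year mortality". It adds an expected pattern, that "women who have the lowest comorbidity burden and also receive RT will experience the greatest improvement in survival outcomes".

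Earlier in the Introduction, the account of the randomised trial says that "no significant survival benefits were observed with the addition of RT to endocrine therapy compared to endocrine therapy alone". The next paragraphs report a survey in which "high proportions of surgeons and radiation oncologists erroneously overestimated survival benefits associated with RT in this group of women".

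Aim 2, Measurements, names the main outcomes as "all-cause mortality and breast cancer-specific mortality considering nonbreast cancer mortality as a competing event". The Aim 2 Statistical Analysis Plan provides weighted Kaplan-Meier curves, weighted Cox models for overall and cause-specific mortality, and weighted subdistribution hazard ratios. Its one stated sensitivity analysis takes two extreme assumptions about censored women. Nonbreast cancer death appears only as the competing event; it is not compared between the RT groups.

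**The concern.** A directional survival hypothesis that departs from the cited evidence needs a reason, and none is given. The practical worry is what would count as support for it. Aim 1, Measurements, accepts that comorbidity affects both survival and the treatment decision. If fitter women are chosen for RT and part of that difference escapes adjustment, all-cause mortality will be lower with RT even if RT does nothing. Residual selection could also produce the expected gradient by comorbidity class, if it differs between classes.

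The Discussion intends the results for shared decision making. A selection effect reported as a survival advantage could feed the overestimation that the Introduction describes. Nothing in the stated Aim 2 analyses would show a reader which explanation is the more likely.

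**Working it through.** **The passages side by side.** The cited evidence applies to RT added to endocrine therapy. The Limitations section says that endocrine therapy is not recorded but assumes that most of the cohort received it. On the protocol's own assumption, then, the evidence applies to most of these women. No rationale for a benefit follows.

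**What the planned tools can show.** Restriction to low-risk disease, weighting, standardised differences and the 24-item comorbidity class all work on recorded variables. The censoring analysis asks a different question. None of them tests for selection that remains after adjustment.

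**Can selection alone give the hypothesised result?** The article states no event rate, RT share or hazard ratio for this cohort, so there is no planned figure to reproduce. Every input below except n=634 and α=.05 is an assumption. With no RT effect, poor health carrying mortality ratio RR, and residual prevalence p1 (RT) and p0 (no RT) after weighting:

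apparent ratio = [1 + p1(RR − 1)] / [1 + p0(RR − 1)]

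| p1 | p0 | RR | Calculation | Apparent ratio |
|---|---|---|---|---|
| 0.15 | 0.25 | 2 | 1.15/1.25 | 0.92 |
| 0.20 | 0.40 | 3 | 1.40/1.80 | 0.78 |
| 0.15 | 0.35 | 3 | 1.30/1.70 | 0.76 |
| 0.10 | 0.40 | 4 | 1.30/2.20 | 0.59 |

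**How large must an effect be to be seen?** Take n=634, assumed 5-year mortality of 8% to 20% (634 × 0.08 = 51 deaths; 634 × 0.20 = 127 deaths) and an RT share s of 50% to 75%. The hazard ratio detectable with 80% power at two-sided .05 is exp{−(1.96 + 0.84)/√[deaths × s(1 − s)]}.

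- 127 deaths, s = 0.50: 0.61.
- 51 deaths, s = 0.75: 0.40.
- Power at a true hazard ratio of 0.8, over the same range: 10% to 24%.

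These figures ignore the variance added by weighting. The effects that this cohort could reliably detect are therefore large, and far from the cited trial result.

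**Can the breast cancer-specific analysis settle it?** With 1% to 3% breast cancer deaths assumed (634 × 0.01 = 6; 634 × 0.03 = 19) and s = 0.60, the detectable hazard ratio is 0.10 to 0.27. That is too sparse to separate benefit from selection.

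**How informative would nonbreast cancer death be?** Subtracting gives about 32 (50.7 − 19.0) to 120 (126.8 − 6.3) deaths. With s = 0.60, the 95% CI around a hazard ratio of 1 is exp{±1.96/√[deaths × 0.24]}: 0.49 to 2.04 at the low end and 0.69 to 1.44 at the high end. This is imprecise, but rests on far more events than breast cancer death does.

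**The case against.** The strongest reply is that the tension is mild and the plan already treats selection as its main threat. Much of this stands.

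- A reader might infer that the background says RT does not improve survival. It says that no significant benefit was seen when RT was added to endocrine therapy. Endocrine use is unobserved here, and the Introduction notes that older women and those with comorbidities are under-represented in trials. The survey is about overestimated benefit, so it does not make every belief in a benefit an error. A benefit in this cohort is not excluded; the article simply does not argue for one.
- The direction of the hypothesis changes no estimate. The plan says "a 2-tailed α level of .05 will denote statistical significance" and reports hazard ratios with 95% CIs.
- It is tempting to say that an all-cause hazard ratio below about 0.8 could not be an RT effect: recurrence of 4% against 1% caps the gain at 3 points, and 1 − 0.03/0.15 = 0.80 or 1 − 0.03/0.25 = 0.88. The documents do not support this. The mortality is assumed, and at 8% the same formula gives 1 − 0.03/0.08 = 0.63. The article gives no time horizon for the recurrence figures, and the step from a risk ratio to a hazard-ratio cutoff ignores sampling error.
- A negative control is not decisive. Comorbidity may confound nonbreast cancer death more than breast cancer death, so an imbalance in the first does not prove bias in the second. A rule that the control must be close to 1 would be undefined and, with the intervals above, too rigid.
- Showing all-cause and breast cancer-specific results together helps somewhat, but the component that most directly shows selection is left out.

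Further bias analyses may sit in a fuller document. The point rests on what this article does state: an unexplained direction, the role given to nonbreast cancer death, and a sensitivity analysis aimed elsewhere.

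**Conclusion.** The concern holds in a limited form. The Aim 2 hypothesis departs without explanation from the evidence that the article cites, and no stated analysis separates an RT benefit from residual selection of fitter women. Under the assumed inputs, selection alone gives apparent ratios of 0.59 to 0.92. Those figures illustrate what is possible; they do not estimate the bias in this cohort. The text does not support saying that the cited trials rule out a benefit, that the plan ignores selection, or that any particular hazard ratio is impossible. This is a worthwhile and inexpensive improvement to interpretation. It does not invalidate the planned models. It also bears on the planned subdistribution hazard ratios, which depend on how competing deaths differ between the RT groups and are hard to read without that comparison.

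**What to change.** 1. In the Aim 2 Statistical Analysis Plan, prespecify nonbreast cancer death as a negative-control outcome. Fit the same weighted cause-specific Cox model to it, overall and, as events allow, by comorbidity class.
2. Report its hazard ratio and 95% CI beside the all-cause and breast cancer-specific results.
3. State beforehand that an all-cause reduction carried mainly by nonbreast cancer deaths will be interpreted as likely residual confounding rather than an RT benefit. Judge this on the estimates and their intervals, without a pass-or-fail cutoff.
4. State the Aim 2 hypothesis as two-sided, or give the reason for its direction against the evidence in the Introduction.

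The cost is one additional model on data already coded, plus a few sentences. The control will be imprecise and open to misclassified cause of death. Reading it this way also assumes that RT does not itself lower nonbreast cancer mortality, which the protocol should state. A favourable all-cause result may have to be qualified.

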## Methods

### Overview

This observational study uses a retrospective cohort design, and the study population comprises older women with low-risk breast cancer who received BCS as a primary treatment and took part in the Medicare Health Outcomes Survey (MHOS). As depicted in Figure 1, the women are first clustered according to their prediagnosis comorbidity burden. Next, we will obtain the propensity score-based probability of receiving adjuvant RT based on observed potential confounding variables. Then, inverse probability weights will be calculated and adjusted for in subsequent analyses. We will examine the effect of RT on 2 outcomes: differences in the patterns of HRQOL trajectories over 10 years post diagnosis and 5-year survival outcomes.

**Figure 1 figure1:**
[figure not shown]
Overview of the proposed retrospective cohort study design. The study population will comprise older women with low-risk breast cancer who received breast-conserving surgery (BCS) as a primary treatment in 1998-2014 and took part in Medicare Health Outcomes Survey (MHOS). The women were first clustered according to their prediagnosis comorbidity burden using latent class analysis. Next, the propensity score-based probability of receiving adjuvant radiotherapy (RT) will be obtained, and inverse probability of treatment weights (IPTW) will be estimated and included in statistical models. To examine the effects of RT on 2 outcomes, health-related quality of life (HRQOL) trajectories over 10-year follow-up periods and 5-year survival outcomes, IPTW-adjusted multilevel growth mixture models and IPTW-adjusted Cox proportional hazards regression models will be used, respectively. The data are sourced from the SEER-MHOS Database. ER: estrogen receptor.

We will utilize the Surveillance, Epidemiology, and End-Results (SEER) database linked to the Medicare Health Outcomes Survey (MHOS) for this project. The SEER-MHOS database resulted from the collaborative efforts of the National Cancer Institute (NCI) and the Centers for Medicare & Medicaid Services. SEER collects data on cancer incidence, treatment, and survival, covering nearly 28% of the United States population. SEER includes high-quality, reliable patient characteristic data (eg, demographics, initial treatment and treatment sequence, tumor characteristics, vital status, and cause of death), while the MHOS data provide patient-reported HRQOL outcomes, comorbidity, functional status, and symptoms for a randomly selected sample of the Medicare Advantage Organization enrollees. MHOS is a longitudinal, 2-wave survey administered twice within a cohort at a 2-year interval. Participants who responded to the first baseline survey may have completed the second follow-up survey. In addition, some participants were sampled in more than 1 cohort, resulting in multiple surveys in different years, which allows the evaluation of HRQOL change over time. Therefore, SEER-MHOS is the best available data source for examining the long-term HRQOL trajectory after diagnosis of cancer in a diverse elderly population with varying degrees of comorbidity burden even though SEER-MHOS is limited in its geographical coverage of the United States.

This study has been approved by the Institutional Review Board of the University of Central Florida (approval number: SBE-18-14238). As individuals who participated in MHOS have provided informed consent to participate in research, this study is exempt from the additional requirements of obtaining informed consent from the study participants [37].

